#### Secondary outcome

Participants’ exercise behavior as well as patterns of MOBIGAME use is analyzed in the intervention group via the app’s usage log. The log can be accessed through each participant’s smartphone to draw conclusions regarding the sustainability of player motivation as well as exercise adherence. The usage data will give information about whether goals of daily PA as well as exercise goals are met, how many workouts are completed, how many workouts are done voluntarily and what influence the suggestions of specific workouts as well as the reminder to be physically active have on players’ exercise behavior. The usage data are further used to analyze which workouts are preferably chosen, which are less popular and whether MOBIGAME use can help players reach and maintain 150 min of moderate PA per week.

In the control group, adherence to the exercise regimen, as suggested during the one-time lifestyle counseling, will be self-recorded by the participants in 24 weekly exercise logs (see above).

Further outcomes are described in detail in Additional file 2.

### Timeline

The duration of the entire MOBIGAME project is 50 months (January 2014 to February 2018). Development of MOBIGAME was completed in February 2016. Recruitment of participants started in January 2016 and is expected to end in June 2017 (18 months). Examinations started in August 2016. The last participant is expected to finish the intervention in December 2017. Altogether, the period between “first patient in” and “last patient out” is 20 months.

### Sample size

Determination of sample size was based on the primary outcome. On the basis of a previous study [43] and our own experience, we assumed that the expected difference in daily PA after 24 weeks between participants in the experimental intervention and those in the control group would be 2500 steps per day. We further assumed that the standard deviation given either study group would be 3000 steps per day [43]. By including daily PA (steps per day) at baseline as a covariate in the analysis, we aim to further reduce error variability and therefore assumed that the correlation between baseline and outcome daily PA will be 0.7. With a significance level of 0.05 (2-sided), the sample size needed to attain a targeted power of 90% for showing superiority of the experimental intervention over control was determined as a total of 34 participants (17 in each group). While we aim to achieve complete capture of all data from all participants, it is unavoidable that some participants will fail to provide outcome data. We will therefore increase the proposed sample size by 20%, so that we will include a total of 42 participants (21 in each group).

### Recruitment

Participants are recruited in cooperation with the Clinic of Endocrinology, Diabetes and Metabolism of the University Hospital Basel, Switzerland as well as on the basis of the database of the Diabetesgesellschaft Region Basel, Switzerland. Further, subjects will be recruited through online and newspaper advertising as well as by word of mouth. Patients who seem to be eligible based on their medical records are contacted via email, telephone or personal inquiry. They then receive a questionnaire via email to verify insufficient levels of PA as well as other general eligibility before an appointment for the first day of examination, including the personal assessment of final eligibility, is scheduled at the Department of Sport, Exercise and Health of the University of Basel.

### Assignment of interventions

#### Allocation and blinding

Participants are allocated at random and in equal numbers to one of the two groups. To achieve this, permuted block randomization with randomly varying block sizes is applied. The randomization list was generated in advance using R version 3.2.3 (R Foundation for Statistical Computing, Vienna, Austria) and the R add-on package blockrand version 1.3 [79] and was transmitted using sequentially numbered, opaque, sealed envelopes [80] by a study assistant not involved in the measurement appointments. Another study assistant receives the envelope on the second visit after all measurements are completed and immediately prior to the distribution of MOBIGAME or the one-time lifestyle counseling, respectively. Through the randomly varying block sizes, which were deliberately not disclosed, study assistants involved in both the measurement appointments and the distribution of MOBIGAME or the one-time lifestyle counseling, respectively, as well as the investigator organizing the appointments cannot know which upcoming participant will be allocated to which of the two groups. All other study personnel and all outcome assessors (with the exception of the telephone interviewers) are blinded with respect to group allocation. No unblinding procedures are intended, except for adverse events that require medical care. A blinding of participants regarding group allocation is not possible. However, to minimize performance bias, participants do not receive detailed information about the other intervention [81].

### Data collection

All measurements of this study are performed by standardized procedures and the assessment staff uses standardized instructions for all measurements to ensure equal testing conditions for all participants. For a description of the study instruments, see study data (above).

To promote participant retention and complete outcome data from all participants, including those who discontinue or deviate from intervention protocols, a total incentive of up to 450 CHF per individual as compensation for their time participating in the study will be provided to all participants. The incentive is not awarded at one time, but is delivered as the participant progresses through the study (150 CHF after completion of the baseline assessment and an additional 300 CHF after completion of the final assessment following the 24-week intervention).

### Data management

To ensure anonymous data handling, sensitive patient data have been previously encoded into a string variable. Data are secured by passwords and only accessible by the responsible staff. The obtained data are digitally stored, backed-up and archived at the Department of Sport, Exercise and Health of the University of Basel. All activity and participant usage data collected by MOBIGAME are stored on the phone’s hard drive and encrypted (and thus secured) with a password chosen by the participant. Entering of this password—and thereby the participant’s consent—is required before exporting these data for analysis post intervention.

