#### Main analyses

The main analyses will be performed on the assumption that missing outcome data are missing at random and therefore will be based on complete cases only.

The primary outcome of daily PA (steps per day) after the 24-week intervention and further outcomes will be analyzed by analysis of covariance (ANCOVA) [83]. The results will be presented as differences in outcome (with 95% confidence intervals) between participants in the experimental intervention and those in the control group, adjusted for the corresponding values at baseline. In the case of chance imbalances at baseline, this will remove a possible bias in the estimate of the effect of experimental intervention over control, while, at the same time, yielding a more precise estimate and accordingly more powerful test for the difference between groups.

Normality will be assessed using normal quantile-quantile plots of the residuals, and to assess variance homogeneity, we will use Tukey-Anscombe plots. If the residual plots indicate departure from model assumptions, suitable transformations of the outcome will be considered [84].

For the secondary outcome, each group will be analyzed descriptively with respect to program adherence.

Finally, correlations between MOBIGAME adherence and acceptance of MOBIGAME (TAM questionnaire score, see Additional file 2) will be analyzed using Spearman’s rank correlation coefficient.

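### Adherence in the app arm is known only for participants whose log is retrieved at the end, and the complete-case rule may make that figure too high

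*Protocol article*

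**What the plan says.** **Storage and export.** The Data management section states: "All activity and participant usage data collected by MOBIGAME are stored on the phone’s hard drive and encrypted". The participant chooses the password, and entering it, which counts as consent, "is required before exporting these data for analysis post intervention". No interim transfer or second copy of the log is described.

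**Use of the log.** The Secondary outcome section states: "The log can be accessed through each participant’s smartphone to draw conclusions regarding the sustainability of player motivation as well as exercise adherence". In the control arm, adherence "will be self-recorded by the participants in 24 weekly exercise logs". The article does not say when or how those logs are collected.

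**Analysis.** The Main analyses section rests on the assumption that "missing outcome data are missing at random and therefore will be based on complete cases only". The same section adds: "For the secondary outcome, each group will be analyzed descriptively with respect to program adherence". It also plans a Spearman correlation between app adherence and the acceptance questionnaire score.

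**Missing data.** The Sensitivity analyses section says that dropouts will be brought in by imputation. It then promises pooled estimates for the primary and further outcomes and does not name the secondary outcome. The Statistical methods section presents this text as the pre-specified analysis plan.

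**The concern.** To retrieve a log after week 24, the study needs contact with the participant, the same phone with the app still on it, a remembered password and willingness to enter it. Someone who enjoys and uses the app is more likely to meet all four conditions. Whether adherence is observed may then depend on adherence itself, which a complete-case summary cannot correct.

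The planned imputation does not clearly help. It is not promised for this outcome. It also assumes that missing and observed values differ only in ways that observed (baseline) data explain, whereas the likely cause of a lost log is disengagement after baseline.

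At stake are the conclusion on sustained motivation and the correlation of adherence with acceptance. Both would describe only participants whose log was retrieved. Adherence is in the trial's title, and the Discussion expects the trial to inform whether a mobile game can address poor programme adherence.

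**Working it through.** **Inputs from the article.** Sample size section: 17 per arm needed, 21 per arm recruited after a 20% increase; difference 2500 steps per day, SD 3000, baseline correlation 0.7, two-sided 0.05, power 90%.

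**Inputs assumed.** Mean adherence among retrieved logs of 60%; adherence among those without a log varied from 0% to 70%. The article gives neither value.

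**The plan's own figure.** Residual SD = 3000 × √(1 − 0.7²) = 2142. With a noncentral t distribution and 2n − 3 degrees of freedom, power is 0.891 at 16 per arm and 0.909 at 17, so 17 per arm reproduces. Then 17 × 1.2 = 20.4, rounded up to 21. The planned loss is 21 − 17 = 4 per arm, or 19%. The sample size is not in dispute; it is used here only for the planned loss.

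**Formula.** Let n be the number randomised to the arm, m the number without a log, a_r the mean adherence in retrieved logs and a_m the mean adherence of those without a log.

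- All-randomised mean = [(n − m) × a_r + m × a_m] / n
- Overstatement by complete cases = a_r − all-randomised mean = (m / n) × (a_r − a_m)

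**Results for n = 21, m = 4, a_r = 60%.**

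| Adherence of those without a log | All-randomised mean | Overstatement (points) |
|---|---|---|
| 0% | 17 × 60 / 21 = 48.6% | 4/21 × 60 = 11.4 |
| 25% | (1020 + 100) / 21 = 53.3% | 4/21 × 35 = 6.7 |
| 50% | (1020 + 200) / 21 = 58.1% | 4/21 × 10 = 1.9 |
| 60% | 60.0% | 0 |
| 70% | (1020 + 280) / 21 = 61.9% | −1.9 |

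**Other losses.** Over the same 0% to 70% range, 2 missing logs give +5.7 to −1.0 points and 6 missing give +17.1 to −2.9. With no missing logs the difference is zero.

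The error is therefore upward only if logs are lost and those who lose them used the app less than the others.

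**The case against.** A reader might infer that the adherence result leaves out everyone who quits and is therefore biased upward. The article does not support that.

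- **Stopping play does not erase the log.** A participant who stops in week 5 but attends the final visit with phone and password supplies a log that shows the low use. The Data collection section seeks outcome data from those who discontinue and pays 300 of the 450 CHF after the final assessment. This stands and narrows the point to logs that cannot be retrieved. It does not remove it: payment is not tied to log export, which needs separate consent.
- **The direction is not established.** A replaced phone or forgotten password need not mean low use. This stands: upward bias is a plausible risk, not a consequence of the text.
- **The size could be overstated.** Setting every lost participant to zero use for 24 weeks is the extreme, since someone lost late may have used the app for months. The article gives no retrieval rate. The fall to 40% adherence by week 20 in the app study cited in the Background says nothing about log retrieval here.
- **Storage on the phone alone is an inference.** The article describes no other copy but does not rule one out.
- **The control arm is less clear.** Nothing is said about how its logs are collected, so the same mechanism cannot be asserted there.
- **Losses will be disclosed.** The Descriptive analysis section promises numbers and reasons for exclusion, including for the secondary analysis. This meets part of the need, but it does not show how far the adherence figure could move.
- **The consequence is limited.** Adherence is summarised within each group without a test, and the password is a consent safeguard that should stay.

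**Conclusion.** The concern holds in a limited form. As described, the app-arm log is exported once, after the intervention, with the participant's cooperation. The stated complete-case rule drops anyone whose log cannot be retrieved, and the article does not say how such participants count towards adherence. Because log loss plausibly goes with low use, the figure may be too high.

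At the planned loss of 4 of 21 and an assumed 60% among retrieved logs, the overstatement is at most 11.4 percentage points. It shrinks to nil as the unobserved use approaches 60% and reverses beyond that. These values illustrate the possible range and do not predict the bias. The primary outcome comes from a separate wristband and is unaffected.

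**What to change.** 1. In each arm, report adherence over all randomised participants, counting weeks without a retrievable log as zero use. Label this a lower bound and show it beside the retrieved-logs-only figure.
2. State that the conclusion on sustained motivation will not rest on the retrieved-only figure alone, and give the number of logs behind the correlation of adherence with acceptance.
3. Ask for a log export, with the same password consent, at any withdrawal contact.

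The cost is a few sentences of plan text, one extra table row and one request at withdrawal. The bound is conservative when a phone or a paper log is lost for reasons unrelated to adherence. Such losses may also differ between arms because the data sources differ. That is why zero use should serve as a bound and not replace the retrieved-only figure as the main result.

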### Statistical methods

The statistical analysis will conform to the pre-specified statistical analysis plan described below. Following the intention-to-treat analysis strategy, participants will be analyzed in the groups exactly as randomized.

#### Descriptive analysis

A flow chart of the participants’ progress through the trial will be used for reporting [82]. The number of screened T2DM patients who fulfill the eligibility criteria and the number included in the primary, secondary and further analyses as well as the reasons for exclusion from these analyses will be reported. Summary statistics will be provided for baseline and outcome data, as appropriate. Continuous variables will be summarized using the mean and standard deviation for normally distributed data or the median and interquartile range for non-normally distributed data. Frequency counts and percentages will be used for categorical data. Visual inspection of box plots of steps per day and further outcomes will be used to identify possible outliers in each group (experimental vs. control) to be excluded in sensitivity analyses.

#### Main analyses

The main analyses will be performed on the assumption that missing outcome data are missing at random and therefore will be based on complete cases only.

The primary outcome of daily PA (steps per day) after the 24-week intervention and further outcomes will be analyzed by analysis of covariance (ANCOVA) [83]. The results will be presented as differences in outcome (with 95% confidence intervals) between participants in the experimental intervention and those in the control group, adjusted for the corresponding values at baseline. In the case of chance imbalances at baseline, this will remove a possible bias in the estimate of the effect of experimental intervention over control, while, at the same time, yielding a more precise estimate and accordingly more powerful test for the difference between groups.

Normality will be assessed using normal quantile-quantile plots of the residuals, and to assess variance homogeneity, we will use Tukey-Anscombe plots. If the residual plots indicate departure from model assumptions, suitable transformations of the outcome will be considered [84].

For the secondary outcome, each group will be analyzed descriptively with respect to program adherence.

Finally, correlations between MOBIGAME adherence and acceptance of MOBIGAME (TAM questionnaire score, see Additional file 2) will be analyzed using Spearman’s rank correlation coefficient.

#### Sensitivity analyses

The effect that any missing outcome data might have on results will be assessed through sensitivity analyses based on imputed data sets. Dropouts (essentially, participants who are lost to follow-up) will be included using imputation methods that allow for the uncertainty about the imputed values. While a few missing values generally present a minor nuisance, a substantial number of missing values is a major threat to a trial’s integrity [85]. If omitting all patients with incomplete data will result in a large proportion of the data being discarded, we will use multiple imputation where missing data are replaced by a set of plausible imputations generated from the patient’s available data [86]. To achieve this, imputation models will need to be developed based on the majority of patients with complete data. Variables included in these models will be carefully chosen, and the study team will discuss whether this choice makes the underlying assumption that any systematic difference between the missing and the observed outcome data can be explained by differences in observed (baseline) data plausible. Rubin’s rules will be used to combine results across ANCOVA models based on the imputed data sets (at least five imputed data sets will be created) and so give an overall estimate of the effect of experimental intervention over control on the primary and further outcomes.

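### Five imputed data sets is too low a minimum for a missing-data check meant for substantial loss; the primary result is not affected

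*Protocol article*

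**What the plan says.** The section Main analyses of the protocol article assumes that outcomes are missing at random. The main ANCOVA models "therefore will be based on complete cases only". The section Sensitivity analyses then says: "The effect that any missing outcome data might have on results will be assessed through sensitivity analyses based on imputed data sets". It goes on: "If omitting all patients with incomplete data will result in a large proportion of the data being discarded, we will use multiple imputation". Results are to be pooled by Rubin's rules, and on the number of imputations the text says "at least five imputed data sets will be created". The procedure covers the primary and the further outcomes. No degrees-of-freedom formula is named, and no 5% decision rule is attached to the pooled result.

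The section Sample size gives the planned loss: 34 evaluable participants are needed, and the plan is to "increase the proposed sample size by 20" per cent, giving 42 randomized (21 per arm).

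**The concern.** Multiple imputation adds random noise of its own, because a finite number of imputed data sets (m) is drawn from a random seed. This noise grows with the share of information that is missing and shrinks as m rises. The plan combines a low minimum for m with a trigger that calls on imputation when much is missing.

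The purpose of the check is to see whether the result moves once incomplete participants are brought in. If the seed alone can move the estimate by a visible fraction of its standard error, a reader comparing the imputed with the complete-case result cannot tell a missing-data effect from chance in the imputation draws. The error can go either way: a false alarm or false reassurance.

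**Working it through.** **Inputs from the section Sample size:** difference 2500 steps per day, SD 3000, baseline-outcome correlation 0.7, two-sided alpha 0.05, power 90%, 17 evaluable and 21 randomized per arm.

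**Assumptions not in the article:** the planned loss is realised as 42 − 34 = 8 missing (8/42 = 19%), at random and equal by arm; imputation uses arm and baseline only; pooling uses small-sample (Barnard-Rubin) degrees of freedom.

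**Step 1: the plan's own figure.** The residual SD is 3000 × √(1 − 0.7²) = 3000 × √0.51 ≈ 2142. The normal approximation gives 16 per arm. The noncentral-t version for ANCOVA gives power 0.891 at 16 and 0.909 at 17 per arm, so 34 in total is reproduced. Then 34 × 1.2 = 40.8, which becomes 42 with equal arms.

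**Step 2: noise in the estimate.** Relative to the standard error, the between-seed SD is about √(missing-information fraction / m). With a fraction of 0.21:

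- m = 5: √(0.21/5) ≈ 0.20
- m = 20: √(0.21/20) ≈ 0.10
- m = 50: √(0.21/50) ≈ 0.065
- m = 100: √(0.21/100) ≈ 0.046

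Simulation agrees (0.20, 0.10, 0.064, 0.045). The planned standard error with 17 per arm is about 2142 × √(2/17) ≈ 735 steps. The noise is therefore about 0.20 × 735 ≈ 147 steps per day at m = 5 and 0.064 × 735 ≈ 47 at m = 50.

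**Step 3: a near-threshold result.** Simulated data sets had complete-case t = 2.15 (p about 0.04) and 4 of 21 missing per arm.

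| m | Between-seed SD of t | p, 5th to 95th percentile | Runs with p < 0.05 |
|---|---|---|---|
| 5 | 0.26 | 0.017 to 0.12 | 56% |
| 20 | 0.13 | 0.026 to 0.070 | about 70% |
| 50 | 0.08 | 0.031 to 0.057 | about 81% |

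**Step 4: dependence on the complete-case p.** With 8/42 missing, the average share of seeds on the less common side of 0.05 is:

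| Complete-case p | m = 5 | m = 20 | m = 50 | m = 100 |
|---|---|---|---|---|
| 0.03 | 33% | 10% | 1% | 0.2% |
| 0.04 | 45% | 32% | 21% | 13% |
| 0.05 | 40% | 39% | 35% | 28% |
| 0.07 | 20% | 6% | 1% | 0% |
| 0.10 | 6% | 0.1% | 0% | 0% |

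At m = 5 the share is also 6% for p = 0.01 and 17% for p = 0.02, but only about 0.1% for p = 0.001. It depends on the loss as well: at p = 0.03 and m = 5 it is 6% with 2/42 missing, 14% with 4/42, 33% with 8/42 and 40% with 12/42.

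**Step 5: how often this would arise.** At the planned effect, the share of trials in which two seeds disagree about p < 0.05 is:

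| Missing | m = 5 | m = 20 | m = 50 |
|---|---|---|---|
| 4/42 | 3% | 1% | 1% |
| 8/42 | 8% | 3% | 1.5% |
| 12/42 | 15% | 5% | 3% |

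A repeat of the 8/42 case gave about 7 to 8% at m = 5 and about 2% at m = 50. With half the planned effect (1250 steps) and 8/42 missing, the rates are about 11%, 6% and 3%.

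The simulations are modest (15 data sets × 200 seeds per cell in step 4, 600 trials per setting in step 5), so the figures are approximate.

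**The case against.** A reader might infer that a re-run could reverse the trial's conclusion. The article does not support that. The primary analysis is complete-case ANCOVA, which involves no random draws. Imputation is a conditional sensitivity analysis whose stated product is an overall effect estimate, with no significance rule. A change of side also needs a result near the threshold, whereas the planned t is 2500/735 ≈ 3.4. Step 3 is therefore a selected case, and step 5 is the fairer overall measure.

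A reader might also blame the small trial. The relative noise depends on the missing-information fraction and on m, not on the sample size.

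A third inference is that intervals will be too narrow, because classical degrees of freedom at m = 5 have a median of about 102 against 23 for Barnard-Rubin (critical t 1.98 against 2.07, an interval about 4% narrower). The article names only Rubin's rules, so it does not show that the classical formula is planned.

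It is also fair that the wording permits more than five imputations, that the seed and final m may be left to a fuller plan, and that good auxiliary predictors would lower these figures. All of this limits the point. What remains is that the article itself states the minimum, an analyst using exactly five would comply, and the trigger directs imputation to the cases where five is least adequate.

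**Conclusion.** The point holds as a minor one. With the planned loss realised and imputation from arm and baseline only, five imputations leave seed noise of about 0.2 standard errors in the pooled estimate. The sensitivity p-value can then fall on either side of 0.05 when the complete-case p is roughly 0.01 to 0.10. At the planned effect this affects about 7 to 8% of trials, against about 2% at m = 50. With less loss or a clear result the effect is small. The primary conclusion is untouched; what suffers is the reliability of the missing-data check as a comparison with it.

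**What to change.** In the section Sensitivity analyses, replace the minimum of five with at least 50 imputed data sets, and set and record the random seed before the analysis. Raising m from 5 to 50 cuts the seed noise about threefold (√10 ≈ 3.2). The pre-set seed does not reduce the noise, but it makes the result reproducible and removes any choice between runs. Naming Barnard-Rubin degrees of freedom, with complete-data value 42 − 3 = 39, is a sensible companion choice.

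The cost is one line of text and seconds of computing; the primary analysis does not change. A result very close to 0.05 stays somewhat seed-dependent even at m = 50 (about 21% of seeds on the less common side at complete-case p = 0.04). The check is therefore better read on the shift in the estimate and its interval than on which side of 0.05 it falls.
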